**J. Attention Monitoring and Psychoeducation Group (“Healthy Lifestyles”) defined:** The HEALTH EDUCATION components (labeled as “Health Education” to participants) are similar to those employed in previous primary care based quality improvement/Chronic Care Model Interventions (patient education [psycho-education described below], provider training [described in Case Finding and Recruitment], active monitoring and referral [case management, discussed under assessments], physician and nurse education and routine contact with PCP [study design rationale]) (see Table 4 below). This Internet site will focus on assisting parents and adolescents with general information on health living appropriate for age as well as psychoeducation about depression. The psychoeducation is intended to assist participants in determining what depressive illness is and what treatment option exist and increase likelihood of seeking treatment. The HEALTH EDUCATION group will receive the same assessments as the CATCH-IT 3 group (including notification and referral) and routine contact with PCP (anticipated 2-3 visits). Psychoeducation Internet site use will be monitored to compare with use of the CATCH-IT 3 intervention as an attention control. Self-harm risk will be managed based on a standard protocol. If study staff are unable to reach participants by phone on the first attempt for any of the above mentioned study procedures, staff will attempt to call two (2) more times over a 1-2 week period to establish contact. If no response is received, staff will try contacting participants by a secondary method as specified in the General Information Sheet (email, mail, or text message). Staff will then wait 2 weeks before contacting the participant again. This process will be repeated until contact with the participant is made or the participant requests to be withdrawn from the study. If withdrawal is requested, a letter confirming their withdrawal will be sent. Details regarding contact of participants and withdrawal procedures can be found in the **Protocol for Contacting Participants** and **Withdrawal Procedures**.

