**Trans-theoretical Model Scale** - We will measure motivation to change risk-factor behaviors before, during, and after the intervention. We adapted the standard approach for measuring motivation as described by Miller and Rollnick to evaluate importance (“rate the importance of preventing a depressive episode”), self-efficacy (“rate your ability to learn coping skills to reduce your risk of depression”) and readiness (“rate your readiness to learn coping skills”) on a 1-10 scale (1, “not important”, 10 “very important”).

**Child’s Report of Parental Behavior Inventory (CRPBI)** – A scale used to evaluate a teen’s perceptions and experiences of both mother and father.

**Sibling Inventory of Differential Experience (SIDE)** – A scale to measure a teen’s perceptions of parent (both mother and father separately) responses to the teen as compared to their siblings.

**Motivational Interview Pre-Measure** - This measure is administered to adolescents prior to meeting with the physician for a motivational interview. It contains items asking adolescents to identify goals for the intervention, consider how they are feeling and their degree of motivation to change their feelings, and their willingness to engage in the present intervention. This is an optional measure.

**Suicide Ideation Scale** - A scale used to assess the adolescent’s current level of suicidal tendencies. This measure is only used in response to adolescent reports of suicidal thinking.

**Suicide Intent Scale** – A measure used to inquire about past suicide attempts. This measure is only used in response to adolescent reports of suicidal thinking.

**Lethality Scale** – A measure of the lethality of past suicide attempts. This measure is only used in response to adolescent reports of suicidal thinking.

**Safety phone calls-** Assessment calls to evidence self-harm ideation and adverse experience with Internet program. Qualitative questions regarding website and baseline interview are also included.

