## ii. Rationale for Selection of Subject:

**Why youth between 13 and 18 years old?** This investigation is limited to adolescents in this age range because our prior experience working with youth and cognitive interventions indicates that children aged 12 and younger may not be able to cognitively grasp the abstract concepts of cognitive-behavioral therapy. Moreover, depression risk has been shown to increase between ages 14 and 18. Therefore, it makes the most sense to target the intervention to adolescents in this risk period.

**Is an Attention Monitoring Psychoeducation comparison ethical and will it provide adequate attention control?** There is currently no standard of care for adolescents who have depressive symptoms but who do not meet criteria for Major Depressive Disorder (MDD). We believe that this study design is ethical because even adolescents in the HEALTH EDUCATION group will receive a higher standard of care than is traditionally available, including (1) screening, (2) psycho-education, (2) monitoring at 1 week and 1, 2, 6, 12, 18 and 24 months for progression to major depression, (3) feedback when progression occurs, (4) referral to the physician and family in completing treatment referrals, and (5) training of the primary care physician to recognize, treat and/or refer adolescents with major depression, consistent with primary care based Chronic Care Model interventions. By providing the HEALTH EDUCATION adolescents with a psycho-education Internet site, tracking assessment calls and physician encounters, we can actually measure "attention" so as to control for or evaluate effects in the mediation analysis. To address physician contact attention, all HEALTH EDUCATION physician contact will be documented. Furthermore, we estimate that the total study contact experienced by both groups when all assessment, PCP and Internet exposure are included to be 6.5 hours in CATCH-IT 3 and 5.0 hours in HEALTH EDUCATION.

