*Specific efforts to minimize risks.* The proposed study poses minimal risks. Those risks that might exist fall into four categories: (a) risks of the preventive intervention; (b) risks associated with research assessments, consisting of face-to-face questions about depression, family and personal functioning, and other mental and emotional problems; (c) risks associated with potential loss of confidentiality; and (d) risks of worsening mental or emotional state. We address each in turn below.

*A) Risks of the preventive intervention.* The Internet-based preventive program consists of 14 modules that teens complete independently. In previous studies we did not find adverse effects of the Internet-based prevention program. However, there is the slight possibility that some teens may find it slightly uncomfortable to think about the feelings and attitudes that are highlighted in the Internet-based program.

*Protection for risks of the preventive intervention:* Youth participating in the Internet-based prevention program will be told that, if they experience any discomfort as a result of their participation, they should discuss any feelings of discomfort with members of the research staff. Research staff will talk with participants about the nature of their discomfort and will encourage them to take breaks or discontinue modules that they find uncomfortable. We will conduct safety surveillance calls for those in the CATCH-IT 3 arm at 1 week and 1, 2, 6, 12, and 24 months. Should we be unable to reach a participant at two consecutive time points, we will utilize public records or locator services to attempt additional contact to ensure the safety of the family.

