*Protection for risks associated with potential loss of confidentiality.* Data for all participants will be kept strictly confidential, except as mandated by law. All research files are kept in locked file cabinets or a locked file room. Participants will be assigned a numerical code for identification in the files. Names and other identifiers will be kept in separate locked files. Statistical analyses will be performed on aggregate-level data; participants are never individually named. All audio-recorded assessments and motivational interviews will be kept in locked file cabinets and will never be played for anyone who is not a member of the research team.

D) *Risks of worsening mental or emotional state and or self-harm thoughts/events.* Some youth enrolled in the Internet-based prevention program, and in the control group, will likely develop depression, suicidal behavior, and/or other mental and emotional problems during the study period. The development of suicidal ideation during the study remains as the most serious risk. However, these are risks inherent in the population and would occur whether or not they were enrolled in the study. We do not believe that the risk of these depressive, suicidal, or other adverse outcomes are increased as a function of being enrolled in this study. Should mood worsen or thoughts of self-harm develop (i.e. teen develop MDD, MDE, or suicidal thoughts), the teen's physician and parents will be notified. Physicians will be recontacted 1 week after disclosure to inquire as to whether the teen has begun treatment or a treatment plan is in place. Should no plan/treatment yet be established, PI or Project Manager will discuss with doctor the best course of action for the teen to ensure their safety and connection to mental health services.

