*Protection against risk of self-harm thoughts/acts:* We have developed detailed procedures for detecting, assessing and triaging youth with psychiatric emergencies. The most frequent, although rare, of these crises involves suicidal behavior (not surprising given the depression risk of these youth) but includes acute substance abuse, psychotic symptoms, and so on. To address the risk of suicide we will conduct safety surveillance calls for those in the CATCH-IT 3 arm at 1, 4, 8 week and 6, 12, 18 and 24 months. We will also conduct post-study monitoring by telephone at 12 and 24 weeks. Monitoring during the intervention will include follow-up phone calls from the study coordinator four weeks after enrollment to assess for suicidal ideation and/or worsening depression symptoms. We will reassess for suicide risk and Major Depression at the exit interview. Because of our extensive and repeated assessment procedures, we believe we will be aware of suicidal thoughts/intentions, should they exist, and we are well prepared to manage these issues. In fact, given the high incidence of suicidal thinking among adolescents, it is likely that participants in this study with suicidal thoughts will be *more* likely to receive appropriate referrals, treatment and follow-up than will adolescents who

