#### **Benefits of study:**

The benefits of participation in this study include having extensive and repeated psychiatric assessments and a referral for treatment if there is a worsening of symptoms. For half of the sample, an Internet-based preventive intervention will be provided at no cost to the family. Both the adolescents and their parents likely will derive a sense of altruism, accomplishment, and contribution by furthering understanding of the problem through their participation. The intervention provided in this study may help to improve adolescents' academic, social, and family functioning and may prevent the development of substance abuse and lower the risk for suicidal behavior. In addition, adolescents and their parents will be paid for their participation.

**Importance of the knowledge to be gained:** The results of this study are important because they will help to develop the guidelines for preventive intervention with youth at risk for the development of depressive disorders, which is a major public mental health concern. The study addresses a pressing social need, the development and evaluation of low cost, evidence based, culturally acceptable and geographically accessible depression prevention interventions for youth. Furthermore, it addresses an important scientific question thus far not addressed in the depression prevention literature: how can youth at-risk for depression be motivated to participate in preventive interventions and change behaviors that may increase their risk? This study addresses this question directly by comparing a motivational approach that includes two primary interviews

and four motivational phone calls with a control condition that includes only a referral to the Internet-site (but with the same telephone monitoring).

Major Depression is a common disorder that causes significant morbidity, lost productivity and is associated with an increased risk of suicide. The first episode usually occurs in adolescence. There are currently no widely available, low cost, effective and acceptable depression prevention interventions for adolescents. The development of a feasible, cost-effective preventive intervention for this age group would be of great value.

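### Self-harm safety calls are assigned to the CATCH-IT 3 arm, on two schedules that disagree at month 18, while the ethical rationale promises controls the same contacts

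*Protocol*

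**What the plan says.** Section 4.g describes the safety surveillance calls twice.

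- Under protection against risk of self-harm thoughts/acts: "we will conduct safety surveillance calls for those in the CATCH-IT 3 arm at 1, 4, 8 week and 6, 12, 18 and 24 months".
- Under protection for risks of the preventive intervention: "We will conduct safety surveillance calls for those in the CATCH-IT 3 arm at 1 week and 1, 2, 6, 12, and 24 months".

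The self-harm paragraph also mentions "follow-up phone calls from the study coordinator four weeks after enrollment to assess for suicidal ideation and/or worsening depression symptoms", without naming an arm.

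Other parts of the protocol describe what controls receive, or list the calls without an arm:

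- Rationale for Selection of Subject, arguing that the comparison is ethical, credits HEALTH EDUCATION adolescents with "monitoring at 1 week and 1, 2, 6, 12, 18 and 24 months for progression to major depression".
- Section 4.e, J (control group defined): "The HEALTH EDUCATION group will receive the same assessments as the CATCH-IT 3 group (including notification and referral".
- List of Assessments, Adolescent Measures, describes the safety phone calls as "Assessment calls to evidence self-harm ideation and adverse experience with Internet program", with no arm limit.
- Importance of the knowledge to be gained describes "a control condition that includes only a referral to the Internet-site (but with the same telephone monitoring".

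**The concern.** The self-harm paragraph is the operative text on suicide risk, and it names one arm. Yet Section 4.g, item D, which covers both arms, calls suicidal ideation the most serious risk and says of such outcomes that "these are risks inherent in the population and would occur whether or not they were enrolled in the study". A risk that belongs to the population does not justify surveillance tied to one arm. The ethical argument for the comparison also relies on control contacts that the safety section assigns, by its wording, to the other arm.

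Two things are at stake. The first is the safety of control youths. The section on measures to be used keeps suicide items off the computer questionnaires and allows such questions only in person or by phone, so a missing call is a missing opportunity to ask. The second is comparability of adverse-event data. The DSMB plan includes a stopping rule for excess adverse events in either arm, and unequal calling would make detection unequal.

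**Working it through.** The protocol states no figure to reproduce. The check sets the schedules side by side, taking week 4 as month 1 and week 8 as month 2.

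| Source | Arm named | Wk 1 | Wk 4 | Wk 8 | M 6 | M 12 | M 18 | M 24 | Times |
|---|---|---|---|---|---|---|---|---|---|
| 4.g, self-harm | CATCH-IT 3 | x | x | x | x | x | x | x | 7 |
| 4.g, intervention risks | CATCH-IT 3 | x | x | x | x | x | – | x | 6 |
| Rationale for Selection of Subject | HEALTH EDUCATION | x | x | x | x | x | x | x | 7 |
| 4.e, L, phone interviews | both | – | – | x | x | x | – | x | 4 |

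**Disagreement within 4.g.** The two lists of calls differ only at month 18.

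**Can the control contacts in the rationale be routine assessments?** Not all of them. Section 4.e, L places assessments at 0, 2, 6, 12, 18 and 24 months, so week 1 and month 1 lie outside it. Month 18 is a self-assessment with no phone interview.

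**What controls lack if 4.g is read literally.**

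- Self-harm schedule minus phone interviews: {wk 1, wk 4, m 18} = 3 times, or 2 if the four-week coordinator call covers controls.
- Intervention-risk schedule minus phone interviews: {wk 1, wk 4} = 2 times, or 1 if that call covers controls.
- First scheduled phone contact: week 4 or month 2 for controls, week 1 for CATCH-IT 3.

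**Longest interval between scheduled phone contacts.**

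- Self-harm schedule: CATCH-IT 3, 12 − 6 = 18 − 12 = 24 − 18 = 6 months; controls, 24 − 12 = 12 months.
- Intervention-risk schedule: 24 − 12 = 12 months in both arms, so no difference.

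A control who completes the month-18 self-assessment by phone or in person, which Section 4.e, L permits, has a shorter gap.

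**The case against.** The strongest reply is that the texts are complementary. Neither paragraph in 4.g says that controls are denied calls. One can read 4.g as giving the CATCH-IT 3 schedule and the rationale as giving the identical control schedule. Section 4.g also says, just before the self-harm paragraph, that both arms are monitored regularly. On that reading nobody misses a contact, and the defect is that the control schedule sits in the wrong place.

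This reading is possible and may describe practice, but it does not settle the text. The rationale does not say how the contact is made, and it refers to progression to major depression rather than self-harm. Staff working from the self-harm paragraph would find one arm named.

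Other points on that side:

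- The arm label suits the paragraph on risks of the intervention. This is correct, but it does not help the self-harm paragraph.
- CATCH-IT 3 youths have check-in calls at weeks 1 and 4 as part of the intervention, so some early imbalance in contact is intended. However, Section 4.e says the coaching calls serve solely to encourage completion and behavior change, so they do not explain why safety calls should differ.
- The supporting texts vary in strength. The equal-assessments statement and the unrestricted listing of safety calls are indirect. The statement on importance gives interview and call counts that do not match Section 4.e, so it carries less weight. The rationale bears most directly.
- Mitigation is real: phone interviews at months 2, 6, 12 and 24, two to three anticipated primary care visits, the month-18 CES-D, notification within 48 hours of severe symptoms on self-assessment, reassessment at exit and post-study telephone monitoring. None of these schedules a phone contact for controls at week 1 or month 18.
- The separate self-harm prevention protocol is not shown and may fix equal practice. It would not remove the contradiction from this document.

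**Conclusion.** The concern holds. The protocol contradicts itself on whether control youths receive the safety calls, and 4.g contradicts itself on month 18. Under the self-harm paragraph taken literally, controls lack 2 of the 7 contacts, or 3 if the four-week call does not cover them, and have a longest phone interval of 12 months against 6. Under the intervention-risk paragraph they lack 1 or 2 of 6, with no difference in longest interval.

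These counts assume that the arm label is restrictive and that the month-18 self-assessment is done online. They describe the text and are not evidence that practice is unequal. The effect on adverse-event counts cannot be derived from the document. Ascertainment of the primary outcome is unaffected, because the KLIFE is scheduled equally in both arms. The point should be fixed because it concerns suicide-risk monitoring of adolescents, most of them minors, and an ethical commitment to the control group.

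**What to change.** In the self-harm paragraph of Section 4.g, and in the intervention-risk paragraph for consistency, replace the reference to the CATCH-IT 3 arm with participants in both arms. Use one schedule in both places: weeks 1, 4 and 8, and months 6, 12, 18 and 24. State that the four-week coordinator call is the week-4 call for both arms.

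If practice is already equal, this is wording only. If not, the cost for 200 control youths, at an assumed 5 to 10 minutes per call, is:

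- 200 × 2 = 400 to 200 × 3 = 600 calls
- 400 × 5/60 ≈ 33 to 600 × 10/60 = 100 staff hours

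The rationale already commits the study to these control contacts. If the CATCH-IT 3 arm currently follows the six-time schedule, adding month 18 means 200 × 1 = 200 further calls, or 200 × 5/60 ≈ 17 to 200 × 10/60 ≈ 33 hours.

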#### **Benefits of study:**

The benefits of participation in this study include having extensive and repeated psychiatric assessments and a referral for treatment if there is a worsening of symptoms. For half of the sample, an Internet-based preventive intervention will be provided at no cost to the family. Both the adolescents and their parents likely will derive a sense of altruism, accomplishment, and contribution by furthering understanding of the problem through their participation. The intervention provided in this study may help to improve adolescents' academic, social, and family functioning and may prevent the development of substance abuse and lower the risk for suicidal behavior. In addition, adolescents and their parents will be paid for their participation.

**Importance of the knowledge to be gained:** The results of this study are important because they will help to develop the guidelines for preventive intervention with youth at risk for the development of depressive disorders, which is a major public mental health concern. The study addresses a pressing social need, the development and evaluation of low cost, evidence based, culturally acceptable and geographically accessible depression prevention interventions for youth. Furthermore, it addresses an important scientific question thus far not addressed in the depression prevention literature: how can youth at-risk for depression be motivated to participate in preventive interventions and change behaviors that may increase their risk? This study addresses this question directly by comparing a motivational approach that includes two primary interviews

and four motivational phone calls with a control condition that includes only a referral to the Internet-site (but with the same telephone monitoring).

Major Depression is a common disorder that causes significant morbidity, lost productivity and is associated with an increased risk of suicide. The first episode usually occurs in adolescence. There are currently no widely available, low cost, effective and acceptable depression prevention interventions for adolescents. The development of a feasible, cost-effective preventive intervention for this age group would be of great value.

Primary care physicians could provide a “motivational bridge” between at-risk adolescents and self-directed depression prevention programs. From the adolescent perspective, there is currently no systematic approach to connect them with self-directed depression prevention programs. Motivational interviewing can reduce at-risk behaviors in adolescents. In this intervention, the goal is to help the adolescent develop their own intrinsic motivation to reduce their risk of depression. The physician helps the adolescent identify how reducing their risk of depression is closely related to their valued life goals. While there is a strong theoretical rationale for a combined primary care/Internet-based intervention, we do not know whether this approach is feasible or would increase use of Internet-based depression prevention interventions.

